## ABBREVIATIONS

| Abbreviation | Explanation                                                          |
|--------------|----------------------------------------------------------------------|
| AHW/P        | Aboriginal Health Worker/Practitioner                                |
| ACIC         | Assessment of Chronic Care Scale                                     |
| CDE          | Credentialed Diabetes Educator                                       |
| DAS          | Diabetes Attitude Scale                                              |
| DAG          | Directed Acyclic Graph                                               |
| DCS          | Diabetes Confidence Survey                                           |
| DNE          | Diabetes Nurse Educator                                              |
| GLMMs        | Generalized linear mixed effects models                              |
| NDSS         | National Diabetes Services Scheme                                    |
| OS           | Onsite Support – one of three elements of the training program       |
| PSN          | Peer Support Network – one of three elements of the training program |
| RACGP        | Royal College of Australian General Practitioners                    |
| SAHMRI       | South Australian Health & Medical Research Institute                 |
| URID         | Unique Record ID                                                     |

Attachment 17: Distress Protocol Interviews

Attachment 18: Distress Protocol System Assessment

## 1. INTRODUCTION

The Aboriginal Diabetes Workforce Study (the study) involves co-designing, implementing and evaluating an Aboriginal Diabetes Workforce Training Program (training program) with health professionals employed by Aboriginal Primary Health Care Services in South Australia. This study is a direct response to several workforce strategies within the SA Aboriginal Diabetes Strategy 2017-2021 and that remain a priority based on recent discussions with Aboriginal primary health care services workforce.

During 2021, seven Aboriginal Primary Health Care Services across South Australia co-designed the training program with the research team, including the study investigators who were highly engaged and industry partners. Industry partners, Diabetes Queensland and Diabetes Australia and funding body by the NDSS, led the development of the e-learning modules. The training program consists of three elements: 1) Statewide Peer Support Network for Aboriginal Health Workers and Practitioners (AHW/Ps), 2) self-paced e-Learning modules, 3) Onsite Practice Support.

A cluster randomised control design at the service level will be used to evaluate the effectiveness of the training program on knowledge, confidence, attitude, practice and skill related to diabetes management, of health care providers. Health care providers include Aboriginal Health Workers, Aboriginal Health Practitioners and multidisciplinary health care providers working in Aboriginal primary health care services across South Australia. Implementing the training program has the potential to embed a minimum standard of diabetes training across the state and professionally develop and support the Aboriginal Health Worker and Practitioner workforce, vital in managing diabetes in the Aboriginal community.

## 2. BACKGROUND

Noncommunicable diseases account for 70% of deaths globally, with 4% of those deaths attributable to diabetes.[1] Well controlled diabetes is associated with increased longevity and prevention or slowing the progression of diabetes-related complications. Large randomised controlled trials have found that a reduction in HbA1c by 1% is associated with a 10% reduction in diabetes-related deaths, a 25% reduction in microvascular endpoints [2] and up to a 50% reduction in the risk of microvascular complications and cardiovascular events.[3] However, the translation of evidence-based guidelines in real world settings do not achieve the outcomes seen in highly regulated clinical trial settings.

Indigenous populations globally have significantly high rates of type 2 diabetes compared to their non-Indigenous counterparts. In Australia, the Aboriginal and Torres Strait Islander population is no exception. For many, chronic disease risk factors present early in life and lead to type diabetes in early adulthood. Type 2 diabetes is 7 times more likely in Aboriginal and Torres Strait Islander adults compared to non-Indigenous adults[4] and responsible for a large proportion of premature morbidity and mortality. Of those who have diabetes, many live with a high burden of diabetes complications of the heart and blood vessels, kidneys, eyes and nervous system.[5] Diabetes and its associated complications are directly

attributable to high mortality rates, with Aboriginal and Torres Strait Islander adults being 6 times more likely to die from diabetes than non-Indigenous Australians.[4]

With diabetes primarily managed within the community setting by multiple disciplines, it is essential that local primary health care services have a workforce that can deliver a minimum standard of diabetes care. Public health evidence across low, middle and high-income countries has demonstrated that community health workers are effective in improving population health, particularly where health workforce resources are limited and where health disparities are persistent despite well-developed health systems.[6, 7] Australian examples include, Aboriginal health workers managing diabetes through case management [8] and continuous quality improvement [9] approaches in primary care settings achieving a 1% and 0.4% reduction in HbA1c, respectively. Investing in remote area AHW/Ps can reduce the risk of diabetes-related hospitalisations and can result in hospital cost savings [10].

Diabetes is a specialty field of health care practice. Currently there is not a nationally recognised diabetes course that advances AHW/P knowledge and skills in diabetes. AHW/P in primary care services have completed either a Certificate 3 or 4 which is delivered by a Registered Training Organisation. The diabetes component of this training is based on raising awareness, screening and the provision of healthy lifestyle information and is covered over the course of half a day. The next level of diabetes training for AHW/P is a Graduate Certificate of Diabetes Education and Management that qualifies as initial credentialing by the Australian Diabetes Educators Association. This is followed by 1,000 hours of training required for full credentialing and on-going training to remain credentialed. While this is a specialised diabetes pathway that some AHW/P would be interested in, there is a gap in the career pathway for those who deliver diabetes care and are seeking additional knowledge and best practice support, without becoming credentialed diabetes educators. As AHW/Ps are integral to the multidisciplinary diabetes team in Aboriginal primary care services and permanently available and accessible within the community, a comprehensive understanding and practice of diabetes education and management will serve to strengthen the impact of their role.

There is consistent high level, high quality evidence to indicate that multifaceted interventions which focus on local contexts, address barriers and promote engagement with health care providers are more likely to result in adoption of best practice and hence improved outcomes.[11] A multifaceted knowledge transfer strategy can have positive impacts, as it considers a number of factors which may influence the uptake and implementation of best practice, including but not limited to knowledge, skills, attitudes, personal beliefs and social context. A tailored intervention strategy may utilise a combination of educational meetings, training of health care providers, educational outreach, practice facilitation, local health leaders, peer support and audit and feedback.[11] These interventions, individually and collectively, form the building blocks of knowledge transfer and evidence implementation strategies and have been rigorously evaluated. Given that knowledge, skills, attitudes, personal beliefs and social context of the proposed cohort of health care providers are likely to vary, a multifaceted approach will allow for customisation and development of tailored interventions. Such a nuanced approach is critical as barriers to

evidence-based diabetic care is also multi-factorial and there is no “one-size fits all” when developing these interventions.

### **The Intervention: Aboriginal Diabetes Workforce Training Program (training program)**

The training program consists of 3 components (Figure 1):

#### **1) Peer Support Network (PSN)**

A state-wide virtual PSN for Aboriginal Health Workers and Practitioners (AHW/Ps).

#### **2) E-Learning Modules**

Nine self-paced e-Learning modules on the following topics of diabetes care: 1) Introduction; 2) About diabetes; 3) Healthy living; 4) Glucose monitoring; 5) Low and high blood glucose levels; 6) Medicines and insulin; 7) Diabetes-related complications; 8) Support for self-management; 9) Other priority groups

Link to the on-line modules: <https://www.ndss.com.au/about-diabetes/aboriginal-and-torres-strait-islander-peoples/health-diabetes-learning/>

#### **3) Onsite Support (OS)**

Practical support for staff to assist with implementing knowledge into practice within their primary care service.

[figure not shown]

*Figure 1: Diabetes workforce training program*

### **3. AIM & OBJECTIVES**

#### **Aim**

To evaluate the effectiveness of a culturally and contextually informed Aboriginal Diabetes Workforce Training Program (hereafter training program) on Aboriginal primary health care workforce knowledge, attitude, confidence, skill and practice relating to diabetes care.

#### **Objectives**

1. To implement the training program in Aboriginal primary health care services across South Australia.
2. To evaluate the effectiveness of the training program on Aboriginal Health Worker, Practitioner and multidisciplinary team knowledge, confidence, skill, practice and

attitude related to diabetes care, and secondary outcomes relating to quality of diabetes care and patient outcomes.

#### **4. HYPOTHESIS**

It is hypothesized that the primary health care services whose workforce participate in the training program will have:

- a workforce with increased knowledge, confidence, and skills to manage diabetes within the local primary health care setting,
- in the longer-term, improvements in the quality of diabetes care provided and patient biomedical outcomes.

## 5. STUDY DESIGN

The study is a Cluster Randomised Crossover trial with two arms (Group A and Group B) (Figure 2). The Cluster Randomised Crossover trial study design ensures that all participating Aboriginal primary health care services across South Australia will have access to the diabetes training, as opposed to only half the services.

[figure not shown]

Figure 2: Study design

The research will be initiated and led by Associate [name] at Wardliparingga Aboriginal Health Equity, [South Australian Health and Medical Research Institute \(SAHMRI\)](#). SAHMRI is South Australia's flagship independent not-for-profit health and medical research institute. SAHMRI's Wardliparingga Aboriginal Health Equity theme is committed to understanding, monitoring, responding to, and reducing inequity in health and wellbeing among Aboriginal and Torres Strait Islander communities. Project coordination will be delivered from SAHMRI [name]. The research is funded by the Medical Research Future Fund Primary Health Care Research Initiative.

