## Randomisation

Randomisation will occur at the service level. Enrolled health services will be randomised into Group A and Group B. Randomisation and allocation will be undertaken after six months of providing PSN for all enrolled health service sites and prior to commencement of the training program. All enrolled health service sites will be listed, and a statistician will be responsible for randomizing the health service sites into cluster one (Group A participants) or cluster two (Group B participants) using a block size through a computer program for randomisation.

For the intervention assignment; a cluster crossover randomised trial will be employed in this study, as all participants receive the same intervention based on random service site allocation. Participants in the study sites will know which group they have been allocated after completing six months of the PSN, and before commencing the E-Learning module for group A. The project research team will not be blinded to group A or B allocation, only people analyzing the results will be masked/blinded.

**Peer Support Network (months 1-17):** Only AHW/Ps will participate in the PSN. AHW/P participants from both Group A and Group B will participate in the PSN for the entire duration of the study. The PSN will commence and convene for 6 months prior to Group A doing the e-learning modules and the OS. The PSN will run online via Teams, once a month, for 1.5 to 2 hours duration, and will be facilitated by a credentialed diabetes educator (DNE) who is a research team member.

As this is a pragmatic trial, it is understood that AHW/Ps may not be able to attend all PSN sessions due to competing work and/or personal priorities.

The PSN meetings will not be recorded. The PSN Facilitator will record participation in the network.

**E-Learning Modules (10 weeks):** There are 9 self-paced e-Learning modules. Each module takes approximately 1 hour to complete. Ten weeks have been allocated to complete the e-learning modules. All participants will do the e-learning modules. Services will have agreed to allow their staff to use the work computers and internet and to do the modules during work hours. These can also be done from any computer, at any time. The modules can be left and picked up at the same place for convenience during working hours.

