**Onsite Support (minimum of twice over 10-week period):** The OS sessions will occur during the same 10-week period as the e-Learning modules. The OS will be face to face at the primary health care service. The number of OS sessions and what is covered during them will be negotiated between the participants and the OS Facilitator. It is suggested that each service hold a minimum of 2 sessions with the OS Facilitator. OS sessions will be held as a group, if there is more than one AHW/P or multidisciplinary health care providers within the health service. The group sessions will be held with AHW/Ps for the first half of the session and then include multidisciplinary health care providers for the remainder of the session. This format will be assessed and adapted as needed. This format responds to direct feedback during the co-design of the training program.

The OS will be facilitated by a credentialed diabetes educator (CDE) employed by Diabetes SA. The CDE will be a member of the research team.

**Group A:** At the start of month 7, AHW/P and multidisciplinary health care provider participants within the health services randomised to Group A will commence the e-Learning modules and OS, for a duration of 10 weeks. During this time, AHW/Ps from both Group A and Group B will continue to participate in the PSN.

**Wash out period (6 months):** There is a six month 'wash out' period where only the PSN is running. This will occur between Group A and Group B doing the e-Learning modules and participating in the OS.

**Group B:** After the 6-month washout period the participating AHW/Ps and multidisciplinary health care providers within the health services randomised to Group B will commence the e-Learning modules and OS, for a duration of 10 weeks. During this time, AHW/Ps from both Group A and Group B will continue to participate in the PSN.

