## **Data collection timepoints for the primary outcomes**

For the entire study there are seven points in time at which data will be collected. These are labelled T0 (baseline), T1 – T6 in Figure 4 and are referred to in the below outline of data collected. Reason for the training program data collection timepoints are as follows:

- T0- Baseline - groups A & B
- T1 - Measure Effect of Peer Support Network - 6 Months Post Baseline Group A & B (Aboriginal Health Workers and Practitioners only).
- T2 – Measure effect of training program (PSN, Online Modules, Onsite Support) on group A - 8.5 Months post-baseline (data collected on both group A & B).
- T3 – Baseline of group B prior to doing the intervention (data collected on both group A & B), 14.5 months post-baseline.
- T4 – Measure effect of training program (PSN, Online Modules, Onsite Support) on group B post group B undertaking the intervention at 17 months from baseline (data collected on both group A & B).
- T5 – Sustainability of effect of training program on group A 23 months post-baseline, and group B 6 months post commencement of intervention.
- T6 - Sustainability of effect of training program on group A 29 months post-baseline, and group B 12 months post commencement of intervention.

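### The trial is labelled a cluster crossover with a wash-out, but its schedule is a one-way delayed-intervention design; treating Group A as untrained at T4 would dilute the effect by up to half

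*Protocol*

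**What the plan says.** Section 5 (Study Design) states: "The study is a Cluster Randomised Crossover trial with two arms (Group A and Group B) (Figure 2". The reason it gives is that the design "ensures that all participating Aboriginal primary health care services across South Australia will have access to the diabetes training". The Randomisation text in section 10.b repeats the label: "a cluster crossover randomised trial will be employed in this study, as all participants receive the same intervention based on random service site allocation". Section 1 (Introduction) uses another one: "A cluster randomised control design at the service level will be used to evaluate the effectiveness of the training program".

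Section 10.b sets the schedule. From the start of month 7, Group A staff "will commence the e-Learning modules and OS, for a duration of 10 weeks". Then: "There is a six month 'wash out' period where only the PSN is running". Group B follows: "After the 6-month washout period the participating AHW/Ps and multidisciplinary health care providers within the health services randomised to Group B" start the same 10-week course. No second course or return to a control condition is described for either group. The Peer Support Network (PSN) runs throughout for Aboriginal Health Workers and Practitioners (AHW/Ps) in both groups.

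Section 10.c collects T2 (8.5 months), T3 (14.5 months) and T4 (17 months) in both groups. T3 is called Group B's baseline. T5 (23 months) and T6 (29 months) are sustainability measurements; T6 is defined as "Sustainability of effect of training program on group A 29 months post-baseline, and group B 12 months post commencement of intervention". Section 11.a names generalised linear mixed models with exchangeable correlation within centre. It does not say how Group A is classed after T2.

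**The concern.** In a two-sequence crossover, one sequence goes from intervention to control. Here that would require Group A to be untrained again when Group B is trained. The primary outcomes are knowledge, attitude, confidence, practice and skill, which are learned attributes. The protocol gives no evidence that they disappear in six months, and its own T5 and T6 measurements are there to see whether they last. Several features favour retention: the PSN continues through the wash-out for AHW/Ps, the shared resource site stays open until the study ends (section 10.b), and the modules are freely available online (section 14).

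What is at stake is who serves as control for the primary outcomes. Randomised comparisons of trained with not-yet-trained services exist only at T2 and T3. An analyst who took the label and the wash-out at face value would add T4, with Group A as the untrained comparator, and mix a clean contrast with one that carries Group A's residual effect.

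**Working it through.** **Timeline.** Inputs from section 10.b: 6 months of PSN, a 10-week course, 6 months of wash-out, a 10-week course. Ten weeks is 10/4.345 = 2.3 months. The end of Group A's course is 6 + 2.3 = 8.3 months, the start of Group B's is 14.3, and its end is 16.6. These agree with the rounded 8.5, 14.5 and 17 in section 10.c. On the protocol's figures, T4 falls 17 − 8.5 = 8.5 months after Group A's course, T5 falls 23 − 8.5 = 14.5 months after it, and T6 29 − 8.5 = 20.5 months after it. Sustainability is therefore measured in Group A well beyond the 6 months allotted to wash-out.

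**Exposure by timepoint, from the schedule.**

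| | T0, T1 | T2 | T3 | T4 to T6 |
|---|---|---|---|---|
| Group A | untrained | trained | trained earlier | trained earlier |
| Group B | untrained | untrained | untrained | trained |

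Every service switches once, in the same direction.

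**Expected value of a crossover estimate.** Assume the same true effect d straight after training in both groups, and let r be the share of Group A's effect present at T4. Period effects cancel because each contrast is taken at a single timepoint.

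- T2, A − B: d − 0 = d.
- T4, B − A: d − rd = d(1 − r).
- Average of the two: ½[d + d(1 − r)] = d(1 − r/2).

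The protocol states no r, so the whole range is shown, as multiples of d:

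| r (assumed) | T4 contrast alone | Crossover average |
|---|---|---|
| 0 | 1.00 | 1.000 |
| 0.25 | 0.75 | 0.875 |
| 0.5 | 0.50 | 0.750 |
| 0.75 | 0.25 | 0.625 |
| 1 | 0.00 | 0.500 |

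A generalised least-squares calculation with fixed time effects, exchangeable correlation of 0.1 or 0.5, Group A coded as exposed at T2 only and Group B at T4 only, and the same r at T3 and T4 gave the same crossover values. This held for T2 and T4 alone, for T0, T2, T3 and T4, and for T0 to T4. The T2 contrast alone equals d at any r.

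**Does coding Group A as trained from T2 onward solve it?** Only if the effect does not fade. At r = 1 the expected estimate is 1.00. At r = 0.5, using T0 to T4, it is 0.79 (correlation 0.1) to 0.88 (correlation 0.5). Using only T2 and T4 it overshoots, at 1.05 to 1.25. A constant-effect model is therefore not a complete remedy.

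**Change from T3.** With r3 and r4 the retained shares at T3 and T4, the second-period contrast of changes is (d − 0) − (r4·d − r3·d) = d(1 + r3 − r4). This equals d when Group A is stable between T3 and T4.

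**The case against.** The strongest objection is that the biased estimator appears nowhere in the protocol. Section 11.a fixes neither period, sequence nor exposure coding, and such coding is commonly left to a statistical analysis plan. The only analysis given an alpha there is one after 12-month follow-up, which is not a T2/T4 crossover contrast. Section 10.c gives T3 as Group B's baseline, which suggests a T3-to-T4 change, and that is not diluted if Group A is stable. Section 1 does not use the crossover label at all. The design figures are not visible, so the reading rests on the text.

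Most of this stands, and it limits the point. A reader might infer that the planned analysis will halve the effect; the protocol does not support that, because it prescribes no crossover analysis and states no retention figure. A reader might also infer that Group A can never lose its training effect, or that a wash-out and a sustainability follow-up are logically incompatible. Both go too far. Partial or full fading is possible, and T5 and T6 ask whether the effect lasts without asserting that it does.

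The objection does not rescue the label. The schedule is one-way on any reading, and nothing in the protocol shows that Group A is untrained again at T3 or T4.

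**Conclusion.** The stated design is wrong as written. The schedule describes a delayed-intervention (wait-list) cluster randomised trial, and the wash-out premise is unsupported and sits badly with the protocol's own sustainability measurements. That conclusion needs no assumption beyond the schedule.

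The bias is conditional on an analysis that follows the label and treats Group A as untrained at T4. In that case any r above 0 pulls the estimate towards zero, by a fraction r/2: nothing if the effect is wholly lost, 25% at half retention, 50% at full retention. The size rests on an assumed r and on equal immediate effects in the two groups. Group A versus Group B at T2 is free of carry-over whatever r is.

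**What to change.** In sections 5 and 10:

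- Rename the design a delayed-intervention (wait-list) cluster randomised trial, align section 1 with it, and call months 8.5 to 14.5 a retention period.
- Name Group A versus Group B at T2 as the primary randomised contrast, adjusted for the T0 score. Use T1 only where it is collected. Section 10.c limits T1 to AHW/Ps, while Table 3 lists all participants at T1 and Table 2 gives multidisciplinary staff seven surveys; these need reconciling.
- State that for AHW/Ps the T2 contrast estimates modules plus onsite support on top of the PSN, because both groups receive the PSN. It does not estimate the whole programme.
- Use Group A versus Group B at T3 as the randomised 6-month retention contrast.
- Do not class Group A as untrained after T2. In any model over all timepoints, include fixed time effects and let the effect vary with time since training; do not assume it is constant.
- Treat Group B's T3-to-T4 change as supportive, and T4 to T6 as follow-up without an untrained comparator.

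The cost is wording only, since T2 and T3 are already collected in both groups. The downside is that fewer timepoints can support causal claims. The change should be made before outcome data are analysed, so that the choice of contrast cannot look data-driven.
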